#### Assessment of adverse events

Risks associated with this study are minimal. However, some possible adverse events may include bleeding, hematoma, fainting, continuous post needling pain, local infection, and other symptoms. Participants will be asked to report any adverse events during the trial, and these will be recorded on an adverse event report form in the case report form (CRF). Once a serious adverse event occurs, the researcher will terminate the trial and rescue procedures will be initiated at once. A written report to the Ethics Committee should be submitted immediately. The overview of the outcome measurement at different time points is shown in Table 1.

**Table 1 Tab1:**
[figure not shown]
Data collection points

The schedule of enrolment, interventions, and assessments

*MC* menstrual cycle, *PI* pulsatility index, *RI* resistance index

#### Sample size

There is insufficient previous data on endometrial thickness after treatment with EA in infertile women with thin endometrium. Besides, the effect of acupuncture varies with different acupoint selection. The aim of the research was to clarify the effects of EA on thin endometrium in infertile women. Therefore, the change in endometrial thickness will be used as an evaluation index. Based on our pilot study, changes in endometrial thickness of the mid-luteal phase after a 12-week treatment were shown to be 8.30 ± 2.83 mm (*n* = 10) in the electroacupuncture group (EA) and 7.10 ± 1.97 mm (*n* = 9) in the sham electroacupuncture group (SEA). Measurement data of parallel control trials (1:1) will be analyzed statistically using the following formula for sample size estimation:
$$ n=\frac{{\left({Z}_{\alpha }+{Z}_{\beta}\right)}^2\ast 2{\sigma}^2}{\delta^2} $$

With a 5% significance level (*α* = 0.05, two-sided) and 80% power (*β* = 0.2), at least 62 patients should be enrolled in each group and a total of 142 participants will be recruited to allow for a 15% dropout rate.

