The endometrium, a unique cyclic tissue regeneration system, depends on the cyclical growth and regression of blood vessels that supply the endometrium [19]. Previous works showed that angiogenesis which depends on the expression of angiogenic factors (VEGF, FGF, and angiopoietin families) is a critical factor in determining the endometrial receptivity during the implantation window (IW) [20]. Thin endometria are characterized by high uterine blood flow impedance, poor growth of glandular epithelium, decreased expression of vascular endothelial growth factor (VEGF), and poor vascular development [21]. Current therapeutic strategies for thin endometrium include long-term administration of exogenous estrogen, low-dose of aspirin, vaginal sildenafil citrate application, transvaginal endometrial perfusion of granulocyte colony-stimulating factor (G-CSF), autologous platelet-rich plasma infusion (PRP), stem cell therapy, vitamins C and E, and L-arginine supplement [8, 22]. Despite the vast diversity of treatment, most of these treatment options result in a minor change in the endometrium thickness and pregnancy rate [22]. Currently, there is no one acceptable approach to treat thin endometrium [23], thus the need for an alternative and complementary therapy for patients with thin endometrium.

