### Inclusion criteria

Patients who conform to the following criteria will be included:
Females, aged between 20 and 45 years;Meets the diagnosis of infertility and is trying to conceive;EMT < 7 mm in the midluteal phase;Willing to participate in this study and sign an informed consent form.

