### Outcome measures

#### Primary outcome

The primary outcome will be endometrial thickness in the mid-luteal phase of the 3rd menstrual cycle (the primary time frame), the 1st menstrual cycle and 2nd menstrual cycle as well as 6 months after completion of the treatment (the secondary time frame) compared with baseline (in the − 1st menstrual cycle).

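### The pilot figures behind the sample size are labelled changes but are credible only as post-treatment thickness, so the 80% power is not shown for change

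*Protocol article*

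**What the plan says.** The Sample size section of the protocol article states that "the change in endometrial thickness will be used as an evaluation index". It then gives the pilot result: "changes in endometrial thickness of the mid-luteal phase after a 12-week treatment were shown to be 8.30 ± 2.83 mm" in 10 women on electroacupuncture, and 7.10 ± 1.97 mm in 9 women on sham. The calculation is set up "With a 5% significance level", "two-sided) and 80% power", and arrives at 62 per group, or 142 in total after a 15% allowance for dropout.

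Two other places bear on how to read these figures. The Inclusion criteria require "EMT < 7 mm in the midluteal phase", and the Participants section gives the same limit. The Primary outcome section says "The primary outcome will be endometrial thickness in the mid-luteal phase of the 3rd menstrual cycle (the primary time frame", to be "compared with baseline" in the cycle before treatment. The article gives no pilot baseline mean, baseline SD, SD of change, or correlation between baseline and final thickness.

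**The concern.** A mean change of about 7 to 8 mm does not fit a population that starts below 7 mm, least of all in a sham arm with neither skin penetration nor current. Thickness after treatment of 8.30 and 7.10 mm, just above the diagnostic limit, fits well. On that reading the two SDs describe final thickness, while the protocol says it is planning for change.

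The SD of a change differs from the SD of a final value, and it can be larger or smaller. The stated 80% power therefore belongs to a quantity other than the one named. Readers could also take sham needling to have added 7 mm, or reuse 2.83 and 1.97 mm as SDs of change when planning or pooling other trials.

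**Working it through.** **1. Inputs from the protocol article, Sample size.** Means 8.30 and 7.10 mm; SDs 2.83 and 1.97 mm; two-sided alpha 0.05; power 80%; 1:1 allocation. The difference is 8.30 − 7.10 = 1.20 mm.

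**2. Reproducing the stated size.** The formula is n = 2 × SD² × (1.960 + 0.842)² / difference², with (1.960 + 0.842)² ≈ 7.849. The simple average SD is (2.83 + 1.97)/2 = 2.40, so n = 2 × 5.76 × 7.849 / 1.44 = 62.79. The stated 62 is this value rounded down; power at 62 is 79.5%. For the total, 62 × 1.15 × 2 = 142.6, against the stated 142. The printed means and SDs are thus the inputs that were used. The question is what they measure.

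**3. Can they be changes?** Suppose the pilot women also entered below 7 mm. The baseline mean is then below 7 mm, and adding 7.10 mm more than doubles it. With an assumed baseline mean of 5 to 6 mm, final means would be 12.1 to 13.1 mm on sham and 13.3 to 14.3 mm on electroacupuncture. Read as final thickness, the figures need no such assumption.

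**4. What this does to the difference.** Under randomisation the baseline means are equal in expectation, so the expected between-arm difference is the same for change and for final thickness. The observed pilot difference could still shift: with an assumed baseline SD of 0.5 to 1.5 mm, the standard error of the baseline difference between 10 and 9 women is SD × √(1/10 + 1/9), or about 0.23 to 0.69 mm. Mainly, however, it is the SD that is in question.

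**5. What this does to the SD.** Take 2.40 mm as the final-value SD, and let b be the baseline SD and r the baseline–final correlation. Then SD of change = √(2.40² + b² − 2 × r × 2.40 × b). Both b and r are assumed, because the article gives neither. The difference is held at 1.20 mm.

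| b (mm) | r | SD of change | n per group | Power at 62 |
|---|---|---|---|---|
| 0.5 | 0 | 2.45 | 66 | 78% |
| 0.5 | 0.7 | 2.08 | 48 | 90% |
| 1.0 | 0 | 2.60 | 74 | 73% |
| 1.0 | 0.3 | 2.31 | 58 | 83% |
| 1.0 | 0.5 | 2.09 | 48 | 89% |
| 1.5 | 0 | 2.83 | 88 | 66% |
| 1.5 | 0.7 | 1.72 | 33 | 97% |

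**6. Where change needs more women.** The SD of change exceeds 2.40 only if b² > 2 × r × 2.40 × b, that is, r < b/(2 × 2.40). This gives r below 0.10 for b = 0.5, 0.21 for b = 1.0 and 0.31 for b = 1.5.

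**7. Baseline-adjusted comparison.** Adjusting final thickness for baseline gives a residual variance of 2.40² × (1 − r²), which never exceeds 2.40². At r = 0.3 the requirement is 62.79 × 0.91 = 57.1, or 58 per group. At r = 0 it is the unadjusted 62.79.

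**The case against.** The strongest reply is that this is a labelling slip with little consequence. The primary outcome is named as thickness in cycle 3, so a calculation on final values is close to it. The expected difference is unaffected, and at moderate correlation the planned size is more than enough for change as well. Much of this stands, and it limits what can be claimed. It does not remove the point: change is named as the index in a separate sentence, the outcome is also set against baseline, and no SD of change is given.

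A reader might infer that the figures can only be final values. The documents do not prove that: they state neither the pilot's entry rule nor its baseline. The Background remark that "most of these treatment options result in a minor change in the endometrium thickness and pregnancy rate" concerns other therapies and adds little. The weight rests on the entry limit and the sham figure.

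A reader might also infer that the trial is too small. The documents do not support that either. The largest requirement, 88 per group, combines the widest assumed baseline SD with no correlation at all between two measurements in the same women. Truncating entry at 7 mm may well weaken that correlation, so low values cannot be dismissed, but nothing shows that they apply.

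How the two pilot SDs are combined is a separate matter. A pooled SD weighted by degrees of freedom is 2.463 and gives 67 per group, but 62 follows from the simple average, so 62 is the benchmark here.

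**Conclusion.** The point holds in a limited form. The planning figures are mislabelled for the variable the section names, and the 80% power is not shown for change. This rests on the pilot having used the same limit of 7 mm. The arithmetic itself reproduces to within rounding.

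The possible effect runs in both directions: about 33 to 88 per group against the stated 62, under the assumed ranges. The upper part applies only if the correlation is below about 0.10 to 0.31. This calls for a correction to the text. It is no evidence of an underpowered trial and does not rank as a fault that must be cured before the plan can stand.

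**What to change.** Check the pilot records to establish what 8.30 and 7.10 mm are.

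- **If they are post-treatment means:** relabel them as mid-luteal thickness in cycle 3. State that the sample size and the 80% power refer to the between-arm difference in that thickness. Define the primary comparison as that difference adjusted for baseline, for example the cycle-3 contrast of the planned linear mixed model with baseline as a covariate. The final-value SD is then a conservative input.
- **If change stays the index:** report the pilot mean and SD of change in each arm and recompute the stated power from them.

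In either case, adding the pilot baseline mean, SD and baseline–final correlation would let readers judge the choice, if paired pilot data exist; the article does not say. Relabelling costs only wording. Naming the baseline-adjusted contrast goes a little further, because it fixes the primary comparison, but it needs no extra women or visits. Keeping change requires paired pilot data and a short recalculation.

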**Methods:**

This study is a randomized, single-blinded, controlled, clinical trial. A total of 142 eligible patients will be recruited and randomly assigned to the electroacupuncture (EA) group or the sham electroacupuncture (SEA) group in a 1:1 ratio. Participants will receive 36 sessions over three menstrual cycles (12 weeks in total), with the same acupoint prescription. The primary outcome of this trial is endometrial thickness in the midluteal phase. The secondary outcomes include endometrial pattern, resistance index (RI) and pulsatility index (PI) of bilateral uterine artery and endometrium blood flow, serum estradiol (E2) and progesterone (P), and pregnancy rate. The pregnancy rate will be evaluated during a 6-month follow-up after completion of the trial. All other outcomes will be evaluated before treatment, during the treatment of 1st, 2nd, and 3rd menstrual cycle, and 6 months after treatment.

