#### Statistical analysis

Statistical analyses of data will be performed using SPSS21.0 software (International Business Machines Corp., Armonk, NY) by analysts who will be blinded to the patients’ allocation. To evaluate the curative effect in this trial, an intention-to-treat analysis (ITT) will be performed. Categorical variables will be presented by frequency (percentage) and analyzed with the chi-squared test or Fisher’s exact test. Continuous variables will be presented as mean ± standard deviation (M ± SD) if they meet normal distribution. Otherwise, they will be presented as medians ± interquartile range (M ± IQR). The demographic characteristics will be compared between the groups by independent *t* tests at baseline. All longitudinal analyses for continuous variables measured at baseline and three-time periods will be performed using linear mixed modeling. Comparisons between the intervention and control groups will be performed using the chi-square test or Fisher s exact test, as appropriate, for categorical variables. To evaluate the safety of acupuncture, we will use a Fisher exact test to report the relative risk of an adverse effect. All the tests will be two-sided, and a *P* value of less than 0.05 will be considered to be statistically significant.

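### Recruiting 142 with 15% dropout leaves about 60 per arm, not the stated minimum of 62, and unadjusted power for 1.2 mm is roughly 75% to 78%, not 80%

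*Protocol article*

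**What the plan says.** The Sample size section of the Protocol article takes its planning values from a pilot study. It reports that "changes in endometrial thickness of the mid-luteal phase after a 12-week treatment were shown to be 8.30 ± 2.83 mm" in 10 women given electroacupuncture, against 7.10 ± 1.97 mm in 9 women given sham. It prints the usual two-means formula, with one common sigma and a difference delta. The error rates are introduced by "With a 5% significance level", two-sided, with 80% power.

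The result is that "at least 62 patients should be enrolled in each group and a total of 142 participants will be recruited", the larger figure being an allowance for 15% dropout. The Methods part of the Abstract repeats the total: "A total of 142 eligible patients will be recruited". The Statistical analysis section also specifies two-sided tests at 0.05.

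The section states neither the value of sigma nor how the dropout allowance was applied.

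**The concern.** The section gives every input except sigma, so the result can be checked. Two steps look wrong, and both lower the sample size.

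- **Dropout.** A total meant to absorb 15% loss should still leave the stated minimum after that loss. This one does not, whatever sigma was used.
- **Common SD.** The formula needs a common variance. The printed 62 is smaller than the formula gives with either usual way of combining the two pilot variances.

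What is at stake is the stated 80% power. If the trial finds no difference, readers will judge that result against this figure, and the plan's own inputs do not support it for a simple two-group comparison at its own dropout rate.

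**Working it through.** **Inputs (Sample size section).** Pilot means 8.30 and 7.10 mm, so delta = 1.20 mm (derived, not printed). Pilot SDs 2.83 (n = 10) and 1.97 (n = 9). Two-sided alpha 0.05, power 0.80, allocation 1:1, dropout 15%. Sigma is not given.

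**Formula (the protocol's own).** n per arm = (1.960 + 0.842)² × 2σ² / δ², where (1.960 + 0.842)² is 7.849 with unrounded normal quantiles.

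**Step 1: reproduce 62.** The simple average of the SDs is (2.83 + 1.97)/2 = 2.40. Then n = 7.849 × 2 × 5.76 / 1.44 = 62.79. That is 62 if cut down and 63 if rounded up, so this is the likely origin of the figure. No other route tried comes as close: one-sided alpha gives 50 to 53, the electroacupuncture SD alone gives 88, and the sham SD alone gives 43.

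**Step 2: combine variances instead of SDs.**

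- Mean variance: (2.83² + 1.97²)/2 = 5.945, SD 2.438. n = 7.849 × 2 × 5.945 / 1.44 = 64.8, so 65.
- Pooled variance: (9 × 2.83² + 8 × 1.97²)/17 = 6.066, SD 2.463. n = 7.849 × 2 × 6.066 / 1.44 = 66.1, so 67.

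**Step 3: reproduce 142.** 124 × 1.15 = 142.6, cut to 142. The allowance was therefore apparently made as n × (1 + 0.15).

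**Step 4: check what 142 leaves.**

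- 142 × 0.85 = 120.7, about 60 per arm.
- To keep 62 per arm: 62/0.85 = 72.9, so 73 per arm, 146 in total.
- The loss that 142 can absorb before falling below 124: 1 − 124/142 = 12.7%.

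**Step 5: power for 1.20 mm, unadjusted two-group comparison.** The normal column is Φ(δ/(σ√(2/n)) − 1.960); the t column uses the noncentral t distribution.

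| Sigma (mm) | 62 per arm, normal | 62 per arm, t | 60 per arm, normal | 60 per arm, t |
|---|---|---|---|---|
| 2.40 (average SD) | 79.5% | 78.9% | 78.2% | 77.5% |
| 2.438 (mean variance) | 78.2% | 77.6% | 76.9% | 76.2% |
| 2.463 (pooled) | 77.4% | 76.8% | 76.1% | 75.4% |

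Every cell is below 80%. With the pooled SD and a t-test at 60 per arm, the difference detectable with 80% power is 1.27 mm.

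**Step 6: consistent totals.** 65/0.85 = 76.5, so 77 per arm and 154 in total; 67/0.85 = 78.8, so 79 per arm and 158 in total.

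**The case against.** **The 62 can be traced to the stated inputs.** A reader might infer that the pilot figures cannot produce 62 at all. They can: the average SD gives 62.79, and the protocol never says that sigma is pooled. This stands. The narrower criticism is that sigma is unstated, that SDs appear to have been averaged where variances should be, and that a minimum was rounded down.

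**The loss of power is small, and one figure would overstate it.** A reader might take the power to be about 75%. That is the low end and needs both the pooled SD and a t-test. The protocol's own normal formula gives 76.1% to 78.2%. This stands too, so the result should be given as a range.

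**The planned analysis is not a completer t-test.** The Statistical analysis section specifies intention to treat and a linear mixed model. The Dropout criteria count poorly compliant women, and women found ineligible after enrolment, as dropouts, and some of them may still supply outcome data. If all 71 per arm did so, t-test power would be 82.2% even with the pooled SD. This limits the conclusion to an unadjusted comparison at the planned loss. It does not repair the paragraph, whose allowance exists to cover that loss and whose formula makes no use of the mixed model.

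**Baseline adjustment might restore 80%.** It might, but the documents cannot say at what correlation. With the pooled SD at 60 per arm, the variance must fall to about 0.89 of its value. If the pilot SDs describe post-treatment thickness, 1 − ρ² = 0.89 requires ρ of about 0.33 or more. If they describe change, as the section's wording says, then with equal variances at both times (1 + ρ)/2 = 0.89 requires ρ of about 0.78 or less. The direction reverses. Means of 7 to 8 mm in women who enter below 7 mm look like post-treatment values, but the text calls them changes, so no threshold can be stated yet.

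**The pilot is the larger uncertainty.** Its difference of 1.20 mm has a standard error of 2.463 × √(1/10 + 1/9) = 1.13 mm and a 95% interval of about −1.2 to 3.6 mm. The Discussion acknowledges the small pilot. This is a fair reason to treat the fault as modest, but not a reason to leave the arithmetic uncorrected.

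**Conclusion.** The paragraph is wrong as written. The dropout error holds for any sigma: at the plan's own 15% loss, 142 leaves about 60 per arm, two short of its own minimum. Separately, 62 is one patient per arm low even with the averaged SD, and 3 to 5 low with the mean or pooled variance.

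Together these put power for 1.2 mm at roughly 75% to 78%, a shortfall of about 2 to 5 percentage points. This rests on a true difference of 1.20 mm, on sigma lying between 2.40 and 2.463 mm, on all 15% of dropouts lacking outcome data, and on an unadjusted comparison.

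A reader might go further and conclude that the trial cannot reach 80% power under its planned analysis. The documents do not support that. They give neither the number of dropouts who will still be measured nor a baseline correlation, so the power of the mixed model cannot be worked out from them.

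**What to change.** Rewrite the Sample size paragraph so that it:

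- states the sigma used, with the pooled pilot SD of 2.46 mm as the natural choice;
- rounds up, giving 67 evaluable women per arm for 80% power by the printed formula (68 by t-test);
- applies dropout as n/(1 − 0.15), giving 79 per arm and 158 in total, or 146 if only the dropout step is corrected;
- if 142 is kept, says that about 60 per arm remain after 15% loss, with about 75% to 78% power for 1.2 mm or, with the pooled SD and a t-test, 80% power for about 1.27 mm;
- says that these figures apply to an unadjusted comparison of women with outcome data.

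The paragraph should also say whether the pilot means and SDs are for post-treatment thickness or for change. Until that is settled, it should rest no power claim on a baseline correlation.

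The cost is rewording one paragraph and a less favourable stated power. Keeping 142 requires no extra patients and leaves the Abstract's total unchanged.

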#### Data management and monitoring

This study will use four levels of data monitoring to improve quality control. A quality controller will check the relevant data in detail on the original CRFs and medical records regularly. The supervision’s main content is whether the initial medical history is accurate, whether the CRF form is real, and whether the correction is standardized. Supervisors will audit the accuracy of registered information, data entry, and outcomes. Any errors required that the audit be repeated from the beginning. The principal investigator will evaluate whether the recruitment and intervention procedures are conducted with rigorous adherence to the protocol. An independent data monitoring committee (DMC) consisting of three experts (an epidemiologist, an acupuncture expert, and a gynecologist) will monitor and evaluate the recruitment of subjects, the progress of research implementation, and the data’s safety, confidentiality, and integrity monthly. DMC will also regularly submit audit reports to the project management department and provide recommendations to continue the clinical trial, modify the trial protocol, or terminate the trial.

#### Statistical analysis

Statistical analyses of data will be performed using SPSS21.0 software (International Business Machines Corp., Armonk, NY) by analysts who will be blinded to the patients’ allocation. To evaluate the curative effect in this trial, an intention-to-treat analysis (ITT) will be performed. Categorical variables will be presented by frequency (percentage) and analyzed with the chi-squared test or Fisher’s exact test. Continuous variables will be presented as mean ± standard deviation (M ± SD) if they meet normal distribution. Otherwise, they will be presented as medians ± interquartile range (M ± IQR). The demographic characteristics will be compared between the groups by independent *t* tests at baseline. All longitudinal analyses for continuous variables measured at baseline and three-time periods will be performed using linear mixed modeling. Comparisons between the intervention and control groups will be performed using the chi-square test or Fisher s exact test, as appropriate, for categorical variables. To evaluate the safety of acupuncture, we will use a Fisher exact test to report the relative risk of an adverse effect. All the tests will be two-sided, and a *P* value of less than 0.05 will be considered to be statistically significant.

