#### Secondary outcome measures

The secondary outcomes include the following four aspects: (1) endometrial pattern, (2) RI and PI of bilateral uterine artery and endometrium blood flow, (3) serum estradiol (E2) and progesterone (P), and (4) pregnancy rate. The first three of the secondary outcomes will be evaluated in the mid-luteal phase of 3rd menstrual cycle (the primary time frame) and the 1st menstrual cycle and 2nd menstrual cycle, as well as 6 months after treatment (the secondary time frame) in comparison with the baseline (in the − 1st menstrual cycle). The pregnancy rate will be assessed during a 6-month follow-up after completion of the trial.

A certified sonographer will measure the endometrial thickness and the first three secondary outcomes through transvaginal ultrasound. A laboratory physician will test the serum estradiol and progesterone through radioimmunoassay. They will be trained and assessed before the trial.

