### Outcome measures selection

Endometrial receptivity plays a vital role in embryo-endometrium cross talk. Endometrium exhibits a short period of receptivity, known as the “window of implantation” [2]. The IW appears in the mid-secretive phase of endometrium on the 20th to 23rd day in the menstrual cycle (namely the 7th–9th day after ovulation) [52]. Therefore, markers of endometrial receptivity are tested in the mid-luteal phase (7 days after the day of ovulation) for a natural menstrual cycle in clinical practice. The ultrasound markers for evaluation of endometrial receptivity are endometrial thickness, pattern, and blood flow impedance [5]. Endometrial thickness as an essential factor in endometrial receptivity is the most extensively used method in clinical practice [53, 54]. Previous research showed a positive correlation between endometrial thickness and implantation rates in 465 cycles of oocyte donation [55]. Endometrial blood perfusion is an important factor for endometrial growth [56]. Resistance and pulsatility index of subendometrial and uterine artery are useful tools for clinicians in predicting endometrial receptivity [57]. High blood flow impedance of uterine radial arteries is associated with poor endometrial growth in patients with thin endometrium [21]. The diastolic flow of the uterine artery in the mid-luteal phase is also associated with reproductive success [58]. Endometrial blood flow directly reflects the microenvironment of embryo implantation. Successful intrauterine implantation is positively associated with lower subendometrial resistance index (RI) and pulsatility index (PI) [59]. In the study, endometrial blood perfusion will be assessed using the PI and RI of bilateral uterine artery as well as endometrium blood flow. The endometrial patterns including type A (triple-line), type B, and type C is classified according to morphology of the endometrium [60]. An earlier study showed that the presence of a triple-line endometrium with a thickness > 6 mm was strongly correlated with conception [61]. The triple line pattern assessed on the day of HCG injection OR IUI was associated with higher clinical pregnancy rates [54]. The endometrium undergoes complex changes in the circulation of estrogen and progesterone (P), which culminate at the mid-luteal phase of the menstrual cycle when it becomes receptive [2, 62, 63]. Serum estradiol and progesterone concentrations may reflect endometrial status [64]. Estradiol stimulates both increases in the size and number of myometrial and endometrial cells as well as changes in endometrial thickness [64]. It is noteworthy that there is a minimum concentration of progesterone which is required to induce normal secretory endometrial development and receptivity [65]. This is supported by a previous study which revealed a significant decrease in clinical pregnancy and live birth rate with serum progesterone level < 10 ng/ml [66].

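### Endometrial pattern is read at baseline, but the only test stated for it leaves that reading unused; adjusting triple-line versus other for baseline would be a small, cheap gain in efficiency

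*Protocol article*

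**What the plan says.** The protocol article, Secondary outcome measures, lists endometrial pattern first among the secondary outcomes. It is to be evaluated in the mid-luteal phase of cycle 3 (the primary time frame), in cycles 1 and 2, and 6 months after treatment, "in comparison with the baseline".

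Outcome measures selection defines the scale: "The endometrial patterns including type A (triple-line), type B, and type C is classified according to morphology of the endometrium". It does not rank B against C. Its only links with conception or pregnancy concern the triple-line pattern.

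Statistical analysis names the chi-square or Fisher's exact test for categorical variables in two places. One describes how such variables are presented and analysed; the other concerns the arms: "Comparisons between the intervention and control groups will be performed using the chi-square test". Linear mixed modelling is reserved for continuous variables. The error rate is common to all tests: "All the tests will be two-sided, and a *P* value of less than 0.05 will be considered to be statistically significant".

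The Sample size section covers endometrial thickness alone: "at least 62 patients should be enrolled in each group". No power is stated for pattern.

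**The concern.** A chi-square or Fisher's exact test between arms at one visit uses the pattern at that visit and nothing else. The baseline pattern, which the trial collects and which the outcome definition refers to, enters no stated analysis. The continuous outcomes listed alongside it do get a model that takes baseline in.

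If a woman's pattern at cycle 3 is related to her pattern before treatment, leaving baseline out keeps avoidable variation in the comparison, and a real difference is somewhat more likely to be missed. Since the trial is sized for thickness only, power for pattern is not assured. What is at stake is precision on one ultrasound marker of receptivity; the primary analysis is untouched.

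**Working it through.** **1. Arm size.** The pilot means differ by 8.30 − 7.10 = 1.20 mm. The simple mean of the two SDs is (2.83 + 1.97)/2 = 2.40. With z values 1.96 and 0.84:

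n = (1.96 + 0.84)² × 2 × 2.40² / 1.20² = 7.84 × 11.52 / 1.44 = 62.72,

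which the protocol gives as 62. Then 62 × 1.15 × 2 = 142.6, given as 142. So 62 evaluable women per arm is the size to use for pattern.

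**2. What the documents do not supply.** They give no A/B/C frequencies, no correlation between baseline and cycle 3, no effect size for pattern and no order of B against C. Everything below rests on assumed values for these.

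**3. Gain from baseline with the contrast held fixed (triple-line versus other).** Three approaches agree.

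- Simulation at 62 per arm, 30/40/30 split, latent correlation 0.3 to 0.7: baseline-adjusted logistic regression gains about 0 to 14 points over the unadjusted test. This covers both a monotone shift and an effect that only moves half of B to A. Type I error is near 5%.
- Simulation with odds ratios 2.5 to 3.0 and latent correlation 0.41 to 0.66: 27–44% unadjusted against 33–50% adjusted, a gain of about 6 points (33 − 27; 50 − 44).
- Approximate hand check, taking a median split of the latent scale. A latent correlation ρ becomes r = (2/π)·arcsin(ρ) between the two binary readings, and adjustment multiplies the expected z by about 1/√(1 − r²). Start from 64.6% unadjusted power (first row of the table below), so expected z = 1.96 + 0.3745 = 2.3345.
  - ρ = 0.3: r = 0.194, factor 1.019, z = 2.380, power = Φ(0.420) = 66%, a gain of about 2 points.
  - ρ = 0.7: r = 0.494, factor 1.150, z = 2.684, power = Φ(0.724) = 77%, a gain of about 12 points.

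**4. What changing the contrast does on its own.** Simulated power without baseline, 62 per arm, 8,000 runs each; percentages are A/B/C:

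| Sham | EA | Three-category chi-square | Triple-line vs other | Ordinal (rank) test |
|---|---|---|---|---|
| 30/40/30 | 50/20/30 | 68.9% | 64.6% | 30.4% |
| 30/40/30 | 50/40/10 | 80.6% | 64.3% | 83.9% |
| 30/40/30 | 50/30/20 | 51.2% | 62.6% | 57.0% |
| 30/50/20 | 50/25/25 | 76.2% | 64.8% | 25.8% |
| 20/40/40 | 40/20/40 | 74.4% | 68.2% | 23.3% |

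Moving from three categories to triple-line versus other changes power by between −16.3 points (64.3 − 80.6) and +11.4 points (62.6 − 51.2). The 0 to 14 points in step 3 is therefore a gain over the unadjusted test of the same contrast, not a guaranteed gain over the planned three-category test.

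**5. The ordinal route.** With an effect running one way over A/B/C, order plus baseline gained about 4 to 27 points over the chi-square test across five splits, latent shifts of 0.3 to 0.7 SD and correlations of 0 to 0.7. Order alone gave at most about 13. When half of B moves to A and C stays put (30/40/30 split), the proportional-odds model with baseline falls to about 31–37%, against about 69% for chi-square.

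**The case against.** The strongest reply is that the planned test is sound. Allocation is randomised, the simulated type I error is about 5%, and an unadjusted test of a secondary outcome is a common choice. Covariates for such an outcome are often settled in a statistical analysis plan, which is not shown, and a journal article condenses. This stands as a limit on severity. It does not remove the point, because the protocol does name the method for categorical variables, and that method has no place for baseline.

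A second reply is that the reference to baseline sits in a schedule covering several outcomes, and that a chi-square test of improved versus not improved would satisfy both sections. That is fair. A reader might infer an outright contradiction between the outcome definition and the test; the text shows only that the use of baseline is not stated.

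A reader might also infer that the chi-square test ignores a graded A/B/C scale and gives away a known amount of power with nothing in return. The documents do not support this. They do not order B against C, they give none of the inputs needed to fix a loss, and the three-category test protects against effects that are not monotone, where an ordinal model does badly.

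Finally, one of the pregnancy links for triple-line relates to the day of HCG injection or insemination, whereas this trial reads pattern in the mid-luteal phase. Support for the A-versus-other contrast is therefore partial, though it is the only contrast the article supports at all.

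**Conclusion.** The point holds as a minor improvement. As written, no stated analysis uses the baseline pattern, although it is collected and the outcome is described relative to it. The planned test is valid, and there is no bias and no effect on the primary outcome.

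The size is roughly 0 to 14 points of power for triple-line versus other, adjusted against unadjusted. It assumes 62 per arm, latent baseline correlations of 0.3 to 0.7 and illustrative pattern frequencies and effects. With weak correlation the gain is close to nothing. No single figure for the loss can be drawn from the documents, and a default proportional-odds model is not warranted on what they say about the pattern types.

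**What to change.** In Statistical analysis, add a sentence for endometrial pattern at cycle 3: logistic regression of triple-line versus other on arm, with baseline pattern as covariate, reporting the odds ratio with 95% CI. Keep the three-category frequencies by arm and the chi-square or Fisher's exact test as descriptive support, so that movement between B and C remains visible. Allow a proportional-odds model only if an A/B/C order is justified before the data are unblinded.

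The cost is a little more analysis work, with no new data or visits. The downside is that the headline contrast narrows to A versus not-A, which in some scenarios has less power than the three-category test before the baseline gain is added.
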